#### Inclusion criteria

Participants who, in line with the following criteria, will qualify for the study are: (1) nulliparous women (18–30 years old), (2) women who meet the diagnostic criteria of PD under the Primary Dysmenorrhea Consensus Guideline [11], (3) women who meet the TCM diagnosis of “*qi* and blood stagnation” or “cold and dampness retention,” (4) women who have normal menstrual cycles (occurring every 28 ± 7 days), (5) a VAS score of the menstrual pain ≥ 40 mm during the baseline menstrual period, (6) women who agree to complete a DD during the study period, (7) women who agree to sign a informed consent form and volunteer for the research.

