### Randomization and allocation concealment

After the screening visit, qualified subjects will be randomly assigned to either the AHP group, the APP group, or the waiting-list group in a ratio of 1: 1: 1. Random numbers will be generated by a third person ([name]) who is not practicing throughout the study, using the random number generator in the SPSS statistical software package (Version 22.0, SAS Institute Inc.). As the letters are drawn (A or B or C), they will be placed into opaque envelopes labeled with sequential numbers. The envelopes will be sealed and remain in numerical order in a safe place until the completion of surgery. The same researcher ([name]) (not involved in the study) will prepare the envelopes. However, it was not possible to conceal the allocation among the waiting-list group.

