No intervention will be performed in the WL group. The participants are required to continue their current living habits, including exercise and diet, while filling out related questionnaires throughout the full observational period of six menstrual cycles. To meet the requirements of the Rule of Ethics, all participant in the WL group will be offered free AHP treatment of their choice at the completion of the study.

With regard to quality control of the herbal plaster, we will take the following measures: (1) first, the herbal plaster will be prepared beforehand by the central pharmacy of the 3rd Affiliated Hospital of Chengdu University of TCM that meets the requirements of the regulatory guidance issued by the China Food and Drug Administration, (2) in addition, pre-job SOP training and examination will be provided by the principal investigator ([name]) to the practitioner for ensuring the quality of treatment procedures (i.e., locate the acupoints, disinfect the skin, attach the plaster on the skin over acupoints), (3) furthermore, the data and results will be monitored by the Evidence-based Medicine Center of Chengdu University of Traditional Chinese Medicine.

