### Sample size calculation

A few scientific trials have investigated the biomechanical effects of acupoint plaster on PD; however, the research methodologies are not appropriate to reference the determination of sample size to this study. The article being used for our study, was from an acupuncture clinical report with the use of VAS scores [16]. Liu’s study reported that patients who received classical acupoint achieved a mean reduction of 36.1 in VAS after acupuncture; while patients who received non-acupoint treatment showed a worse score of 29.9. Therefore, the decrease in VAS score of the three groups was predicted to be 38, 29 and 26, respectively. Using a bilateral test with an alpha value of 5% and a power of 80%, standard deviation for each group was 20 mm. According to the calculation with PASS software (Version 11.0, NCSS, LLC. Kaysville, UT, USA) in a 1:1:1 ratio, the effect size is 0.2550 of 51 participants in each group. The sample size is also calculated using the following formula [58]:$$ n\kern0.5em =\kern0.5em 2{\left(\sigma \frac{z_{1-\alpha /\left(2\tau \right)}+{z}_{1-\beta }}{\mu_A-{\mu}_B}\right)}^2. $$

Allowing for a 15% dropout, the sample size was increased to 60 per group, making a total of 180.

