#### Methods of statistical analyses

Data analyses will be processed with SPSS 22.0 (SPSS Inc., Chicago, IL, USA) and supervised by a skilled statistician blinded to group allocation.

The Full Analysis Set (FAS) is for all participants who have been randomized in terms of the intention-to-treat (ITT), and the per-protocol analysis set (PPS) and is for the individuals who complete the trial and do not have significant protocol violations. On the basis of rule of the last-observation-carried-forward, missing values will be imputed. In order to evaluate therapeutic effect and safety, the FAS and PPS will be used simultaneously.

Categorical data, such as gender and medical history, will be tabulated with frequencies or percentages; and continuous data, such as age and disease course, will be reported as mean ± standard deviation (SD), or median. For the baseline variables, sociodemographic data and other basic indicators will be carried out using analysis of variance (ANOVA) and *χ*^2^. To compare variables before and after treatment in the same group, a paired *t* test will be used. Repeated measures analysis of variance (ANOVA) will be used to compare the intergroup differences among the three groups. Tests of ITT between the AHP and APP arms and between the APP and WL arms with respect to the change will based on time-intervention interactions in the mixed-effect models. A *P* value of less than 0.05 (two-sided) indicates a statistically significant difference, with 95% confidence intervals.

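### Within-group before-after paired t tests are planned as inference, yet on the plan's own predicted falls they would be significant in every arm, including the untreated one

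*Protocol article*

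**What the plan says.** The section on methods of statistical analyses in the protocol article plans a comparison inside each group: "To compare variables before and after treatment in the same group, a paired *t* test will be used". It does not call this test descriptive, and it exempts neither the primary VAS outcome nor the waiting-list arm. The section closes with one rule for significance: "A *P* value of less than 0.05 (two-sided) indicates a statistically significant difference, with 95% confidence intervals".

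The same section also plans between-group analyses. These are a repeated measures ANOVA across the three arms, and mixed-model time-by-intervention tests of AHP against APP and of APP against WL. It does not say which analysis carries the efficacy conclusion.

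Three other places bear on the point:

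- Sample size calculation: "the decrease in VAS score of the three groups was predicted to be 38, 29 and 26, respectively", and "standard deviation for each group was 20 mm".
- Interventions, on the third arm: "No intervention will be performed in the WL group".
- Inclusion criteria: "a VAS score of the menstrual pain ≥ 40 mm during the baseline menstrual period". The study design section adds a run-in of three menstrual cycles to set an individual baseline.

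**The concern.** A before-after test in a single arm asks whether the mean changed. It cannot say why. Whatever would have happened without the plaster is included in the change, and the protocol's planning figures put that untreated course at 26 mm. A test that comes out significant under active treatment, placebo and no treatment alike tells the reader nothing about the plaster.

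What is at stake is interpretation. The Abstract and Discussion say that the three arms exist to separate the specific effect (AHP against APP) from the non-specific effect (APP against WL). A within-AHP P value merges the two again. If AHP and APP turned out alike, a very small within-AHP P value could still be presented as a sign of benefit, because the plan gives it the same inferential standing as the randomised comparisons.

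**Working it through.** **Inputs.** All come from the sample size section unless noted.

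- Predicted falls: 38, 29 and 26 mm. They are assigned to AHP, APP and WL by the article's usual arm order, as in the randomisation section: "either the AHP group, the APP group, or the waiting-list group in a ratio of 1: 1: 1".
- SD 20 mm per group, taken as the SD of the change because the means are decreases.
- 51 per arm evaluable; 60 per arm after 15% dropout.
- Two-sided alpha 0.05.

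**Reproducing the plan's own figure.** The mean of the three falls is (38 + 29 + 26)/3 = 31. The deviations are 7, −2 and −5, so the SD of the means is √((49 + 4 + 25)/3) = √26 = 5.099. Then f = 5.099/20 = 0.2550, as stated. One-way ANOVA power is 79.6% at 50 per arm and 80.5% at 51, so 51 is reproduced. 51/0.85 = 60 is reproduced too. The inputs are therefore being read as the sponsor used them.

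**Paired t test in each arm.** Expected t = fall/(20/√n). The standard error is 20/√51 = 2.80 mm at n = 51 and 20/√60 = 2.58 mm at n = 60.

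| Arm | Predicted fall (mm) | Expected t, n = 51 | Expected t, n = 60 |
|---|---|---|---|
| AHP | 38 | 13.6 | 14.7 |
| APP | 29 | 10.4 | 11.2 |
| WL | 26 | 9.3 | 10.1 |

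Power exceeds 99.99% in every cell. The smallest mean fall that reaches significance is t(0.975, n − 1) × 20/√n, which is 5.6 mm at n = 51 and 5.2 mm at n = 60.

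**If AHP were no better than placebo.** With a fall of 29 mm in both plaster arms, the within-AHP t would still be about 10.4.

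**Sensitivity to the SD.** If 20 mm is the SD of a single score, the SD of the change is 20 × √(2(1 − ρ)), at most 28.3 mm when ρ is not negative. The WL t at n = 51 is then 26/(28.3/√51) = 6.6, and power is still above 99.99%. With a change SD of 40 mm, WL power is 99.5% at n = 51 and 99.9% at n = 60.

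**What the entry threshold alone would do.** The documents give no population mean or between-cycle correlation, so these are assumptions: normal scores with SD 20 mm, mean μ of 40 to 60 mm, and correlation ρ of 0.5 to 0.8. With a = (40 − μ)/20, expected regression to the mean is 20 × (1 − ρ) × φ(a)/(1 − Φ(a)). This gives about 1 to 8 mm, and the paired test at n = 60 would be significant with probability of about 10% to 91%. The threshold by itself guarantees nothing; the near-certainty comes from the predicted falls.

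**The randomised contrasts for comparison.** With SD 20 and no multiplicity adjustment, AHP against APP (38 − 29 = 9 mm) has 62% power at 51 per arm and 69% at 60. Even if the sponsor's predictions are exactly right, there is a 31% to 38% chance that this contrast is not significant, while the within-AHP test would almost surely be.

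**The case against.** The strongest reply is that the efficacy question already sits with the between-arm contrasts. The specific and non-specific effects are defined as AHP against APP and APP against WL, the analysis section tests both, and nowhere is the paired test called primary or said to support a claim of efficacy. A paired t test is also valid for what it tests; only a causal reading would be wrong. This stands, and it limits the point to an extra inference with no proper use in answering the trial's question.

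A reader might infer more than the documents support:

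- *That the trial lacks a controlled comparison, or ranks the within-group test first because it is mentioned before the others.* Controlled comparisons are planned, and the order of sentences sets no hierarchy.
- *That the 40 mm entry criterion makes significance inevitable.* It may add some regression to the mean, less if the three run-in cycles are averaged, but the range above shows that it does not guarantee the result.
- *That significance in the waiting-list arm is a certainty.* It depends on the predicted 26 mm. No derivation is given for that figure: the cited acupuncture study, as described, supplies only 36.1 and 29.9 for two treated groups. The protocol does not attribute the 26 mm to regression to the mean or natural course either.

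Two smaller replies can be made. First, the reference to treatment might exclude the untreated arm from the test. That leaves the problem in AHP and APP, where the test still cannot remove the untreated course. Second, a 95% confidence interval for an arm's mean change excludes zero exactly when the paired test gives P < 0.05. That is correct, so the remedy has to lie in labelling within-arm change as descriptive and in saying where claims may rest. Replacing a P value with an interval would not be enough.

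**Conclusion.** The point holds as an additional uninformative inference. If the predicted falls occur, the paired test is practically certain to be significant in all three arms, and this is robust to a change SD of up to about 40 mm. On the same figures the untreated fall is 26/38 = 68% of the predicted AHP fall and 26/29 = 90% of the predicted APP fall, so most of what the within-arm test detects would not be a plaster effect.

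The conclusion rests on reading the three falls in arm order and on the 26 mm being roughly right. If the untreated fall were only a few millimetres, significance in the waiting-list arm would no longer be assured. The within-arm test would still be unable to separate a plaster effect from the untreated course.

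The randomised comparisons, the sample size and the data are not affected. The consequence is a risk of misreading, made realistic by the 62% to 69% power of AHP against APP. That makes the change worthwhile but of moderate weight.

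**What to change.** In the section on methods of statistical analyses, remove the within-group paired t tests and their P values from the planned inferences. Replace them with two statements:

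1. Each arm's mean change per cycle, with SD or confidence interval, will be reported side by side as description only, the waiting-list arm included.
2. Claims of therapeutic effect rest solely on the randomised between-arm contrasts already planned, AHP against APP and APP against WL.

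The cost is a sentence or two of text. Sample size stays at 51 evaluable and 60 randomised per arm, no data collection changes, and no information is lost. The article reports recruitment as ongoing, so while that is so the change can be made before results are known.

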## Methods/design

### Study design

This proposed study is a single-centered, randomized, placebo-controlled trial which was devised following the Consolidated Standards of Reporting Trials (CONSORT) Statement recommendations [40] and the Standardized Protocol Items: Recommendations for Interventional Trials (SPIRIT) guidelines Additional file 1 [41]. Ethical approval has been obtained from the Institutional Review Board (IRB) of the Teaching Hospital of Chengdu University of Traditional Chinese Medicine (Approval No. 2016KL–003). We registered the study on the Chinese Clinical Trial Registry (Registration No. ChiCTR-IOR-16008701) in 2016.

The study will take place in the 3rd Affiliated Hospital of Chengdu University of TCM. During a run-in period of three menstrual cycles prior to randomization, the patients will be required to complete a Dysmenorrhea Diary (DD) and record related symptom scores every month to establish an individualized baseline score. A total of 180 subjects meeting the including criteria will be allocated randomly to three research groups that include one experimental group of the AHP and two control groups of the acupoint placebo plaster (APP) group and the waiting-list WL group. After randomization, subjects in the AHP and APP groups will receive treatments for another three menstrual cycles. Follow-up assessments through telephone calls or social media smartphone application will be processed for the last period of three menstrual cycles until the completion of study. Altogether it takes 9 months of three stages with three period cycles in each session. (See Fig. 1 for the study flowchart, and Fig. 2 for the assessment schedule).

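### The pairwise VAS tests are specified on change with no baseline covariate, although a three-cycle run-in is collected; baseline adjustment would gain precision, by an amount the document does not let one fix

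*Protocol article*

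**What the plan says.** Under Methods of statistical analyses, the protocol article compares the three groups by repeated measures ANOVA. It then specifies "Tests of ITT between the AHP and APP arms and between the APP and WL arms with respect to the change", based on time-by-intervention interactions in mixed-effect models. No baseline covariate is named, and baseline is not constrained to be equal across arms. Baseline variables are to be compared between groups by ANOVA and chi-square tests.

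Under Study design, participants go through a run-in of three menstrual cycles before randomisation and "record related symptom scores every month to establish an individualized baseline score". How the three cycles combine into that score is not stated. Time points of outcome measurements adds that VAS, CMSS and SF-12 are recorded at baseline and in every treatment and follow-up cycle. Inclusion criteria require "a VAS score of the menstrual pain ≥ 40 mm during the baseline menstrual period".

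Under Sample size calculation, "the decrease in VAS score of the three groups was predicted to be 38, 29 and 26, respectively", and "standard deviation for each group was 20 mm". The article does not say whether that SD is of the change or of the score, or from which baseline.

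**The concern.** With baseline as one of the times, an ordinary time-by-intervention interaction is a difference between arms in mean change from baseline. Subtracting baseline fixes the regression slope on baseline at 1. With equal variances, the slope on a single cycle is the between-cycle correlation, which is below 1 for a pain score that varies from month to month. The subtraction then over-corrects: it adds baseline noise to the contrast and lets chance baseline differences between arms carry through. A covariate lets the data set the slope. Significance tests of baseline balance leave the estimate as it was.

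Precision matters here because AHP versus APP is the comparison that the Discussion section calls the specific effect, and on the article's own inputs it has less than 80% power at the planned size. The material for a more precise analysis is already being collected.

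**Working it through.** **Inputs from the article.** Predicted VAS decreases of 38, 29 and 26 mm, so AHP − APP = 9 mm and APP − WL = 3 mm; SD 20 mm; two-sided alpha 5%; 51 per group, raised to 60 for 15% dropout.

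**Assumptions, not in the article.** Equal variances and equal correlation r between any two cycles (compound symmetry), r = 0.3, 0.5 or 0.7; a single post-randomisation VAS compared by a two-sample test (noncentral t).

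**The article's own figure.** The mean of 38, 29 and 26 is 31. The variance of the means is (49 + 4 + 25)/3 = 26, so f = √26/20 = 0.255, as stated. The three-group F test has 79.6% power at 50 per group and 80.5% at 51, so 51 reproduces. 51/0.85 = 60 reproduces the enrolled number.

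**AHP versus APP on the same inputs.** The noncentrality is 9/(20·√(2/51)) = 2.27. Power is 61.4% at 51 per arm and 68.6% at 60.

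**Variances, as multiples of the single-cycle variance.**
- Change from one baseline cycle: 2(1 − r)
- Change from the three-cycle mean: 4(1 − r)/3
- Adjusted for one baseline cycle: 1 − r²
- Adjusted for the three-cycle mean: 1 − 3r²/(1 + 2r) = (1 − r)(1 + 3r)/(1 + 2r)

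**Case 1: the 20 mm SD is that of change from one cycle.** Each ratio is relative to 2(1 − r).

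| Analysis | Variance ratio | r = 0.3 | r = 0.5 | r = 0.7 | Power at 51 per arm |
|---|---|---|---|---|---|
| Change from one cycle | 1 | 1 | 1 | 1 | 61.4% |
| Adjusted for one cycle | (1 + r)/2 | 0.650 | 0.750 | 0.850 | 79.7 / 73.8 / 68.5% |
| Change from three-cycle mean, no covariate | 2/3 | 0.667 | 0.667 | 0.667 | 78.7% |
| Adjusted for three-cycle mean | (1 + 3r)/(2(1 + 2r)) | 0.594 | 0.625 | 0.646 | 83.2 / 81.2 / 80.0% |

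Averaging the run-in moves power from 61.4% to 78.7%. The covariate then adds 1.3 to 4.5 points.

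**Case 2: the 20 mm SD is already that of change from the three-cycle mean.** The ratio is 3(1 + 3r)/(4(1 + 2r)) = 0.891, 0.938, 0.969. Power goes from 61.4% to 66.4 / 64.2 / 62.8%, a gain of 1.4 to 5.0 points.

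**APP versus WL.** At 3 mm and 51 per arm, power is 11.7% unadjusted. It is 13.9% with one-cycle adjustment and 15.8% with three-cycle adjustment (case 1, r = 0.5).

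**The case against.** A reader might infer that the missing covariate costs the trial its 80% power, or that adjustment would restore it. The document does not support that. Its description of an individualised score built over three monthly recordings may already intend a three-cycle baseline. If the SD refers to change from that baseline, case 2 applies and the gain is a few points. Even in case 1, most of the gain comes from averaging, not from the covariate. The shortfall itself arises because 51 per group was sized on the three-group F test, which is a separate matter.

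A reader might also infer that regression to the mean after entry at 40 mm or more biases the comparison. It does not. All arms pass the same threshold before randomisation, so the difference in change is unbiased, and chance imbalance is already counted in its standard error. What is lost is efficiency.

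Two further limits stand.
- The formulas ignore the entry threshold, which narrows the baseline distribution. As an assumed illustration, take a pre-selection VAS that is normal with mean 60 and SD 20, and apply the 40 mm threshold to the single baseline cycle. Case 1 then falls to about 77–78% with three-cycle adjustment and 66–74% with one-cycle adjustment.
- The 61% is for a simple two-sample test at 51 per arm, not for the planned repeated-measures model in all randomised participants.

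Finally, the article never uses the word unadjusted, and covariate lists are often left to a fuller plan. That is fair as to detail. But the article does name the quantity tested (change) and the model term that tests it, and as written these describe a contrast with no baseline adjustment.

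**Conclusion.** The point holds as a recommendation on efficiency. The planned test is valid. Under the stated model, baseline adjustment is never less efficient for any correlation below 1, apart from the degree of freedom it uses, so the direction is secure.

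The size is not. At 51 per arm, AHP versus APP power goes from about 61% to 63–66% if the 20 mm SD is change from the three-cycle mean, and to about 80–83% if it is change from one cycle. In the second case averaging alone gives about 79%, and the covariate contributes only about 1 to 5 points in either case. These figures rest on compound symmetry, r = 0.3 to 0.7, no truncation at entry and a simple two-sample test. Adjustment leaves APP versus WL badly underpowered and leaves the omnibus sample size out of step with the pairwise tests.

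**What to change.** In Methods of statistical analyses, or in the analysis plan before unblinding:

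- State that the individualised baseline score is the mean of the three run-in cycles.
- Analyse post-randomisation VAS in the mixed model with that baseline, and its interaction with cycle, as covariates. Do the same for CMSS and SF-12.
- Report baseline characteristics descriptively and drop the between-group significance tests.
- State in the sample-size section what the 20 mm SD refers to, so that the expected gain can be judged.

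The cost is a few lines of text. If the run-in scores are recorded each month as described, no patients, visits or measurements are added. Recruitment was ongoing when the article was written, so the change could be dated and documented before allocation is revealed.

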**Methods/design:**

This study is a randomized, single-center, placebo-controlled clinical trial. A total of 180 women with PD will be included and randomly allocated to the AHP, APP and waiting-list (WL) groups in a 1:1:1 ratio. Patients in the AHP group will be provided with herbal plasters (*Shaofuzhuyu* decoction) on various acupoints: *Shenque* (CV8), *Guanyuan* (CV4), *Qihai* (CV5), *Ciliao* (BL32) and *Zigong* (EX-CA1). Women in the APP group will receive placebo plasters on the same acupoints, and no intervention will be given to the WL group until completion of the study. The primary outcome will be pain intensity reduction measured by a Visual Analog Scale (VAS), with other outcome measurements including the Cox Menstrual Symptom Scale (CMSS), the 12-Item Short Form Health Survey (SF-12) and the Participant Global Impression of Change (PGIC). All assessments will be performed at baseline, each menstrual cycle during the treatment course and the follow-up course. Any adverse events will be recorded throughout the study.

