#### Secondary outcomes

The secondary outcomes include the Cox Menstrual Symptom Scale (CMSS) [50], the 12-Item Short Form Health Survey (SF-12) [51], the Participant Global Impression of Change (PGIC) [52] and the DD.

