#### Time points of outcome measurements

The VAS, CMSS, SF-12 and DD will be recorded at baseline and at every menstrual cycle throughout the treatment and the follow-up periods. The PGIC will be measured at the first, second, third, fourth, fifth and sixth menstrual cycles after inclusion.

We will estimate the expectation of participants to determine whether their expectations affected the outcomes by using the Credibility Expectancy Questionnaire (CEQ) [53, 54] at the baseline and the first to the third menstrual cycle before receiving treatment. In the proposed study, the questionnaire will be used to control for placebo effects, which are expected to be relatively high for light-therapy studies [54]. Blinding will be assessed by asking participants what group they thought they were in (AHP group or APP group, or “don’t know”) at the end of trial, and why they believed that they were in that group.

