## Discussion

Currently, there have been no methodologically controlled clinical studies confirming the efficacy of AHP therapy. To meet the demand for high-quality RCTs, our team has designed this randomized placebo-controlled trial to explore the potential therapeutic effect of the AHP for PD. In this pilot study, we will compare the change in menstrual pain after administration of three interventions: the active intervention (AHP), the placebo intervention (APP), and a period of no intervention (WL). This three-arm RCT aims to investigate the relative contributions of the specific (AHP vs. APP) and the non-specific (APP vs. WL) effects to the overall clinical effects of the AHP on women with PDM. In particular, a growing body of studies [58, 59] has confirmed that the sham control may play a crucial part in evaluating the effectiveness of a treatment, which may help separate the specific and non-specific effects. Therefore, the active and sham acupoint plasters should be adopted to investigate the specific analgesic effect on patients with PDM. In order to minimize the placebo effect, buckwheat flour paste is used in the placebo arm, which may successfully blind the patients and the practitioners due to their identical appearance. For the purpose of comparing the non-specific (sham intervention vs. no treatment) effects and avoiding bias caused by psychological influences, we set the third group of the waiting-list control without any acupuncture interventions. This is because participants in the APP group may have a placebo effect due to the unawareness of group allocation and the treatment that they are undergoing; therefore, placebo effects may happen secondary to their strong beliefs of being in the AHP group.

To our knowledge, the present study will be the first clinical trial that compares the AHP with the APP, and being placed in a waiting-list control group in treating PD. The scientific and rigorous methodologic design of this trial hopefully will provide consolidated evidence on the efficacy and safety of the AHP for treating PD, and hopefully provide reference to clinical practice Additional file 2.

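### If the plan's only pairwise rule, the time-by-intervention interaction, is applied to PGIC, which has no baseline, it tests drift over cycles 1-6 and misses a constant benefit

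*Protocol article*

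**What the plan says.** The section on methods of statistical analyses gives two between-group analyses. One is an overall comparison: "Repeated measures analysis of variance (ANOVA) will be used to compare the intergroup differences among the three groups". The other is the only rule for pairwise comparisons. It covers AHP against APP and APP against WL, by intention to treat, and says that these tests "with respect to the change will based on time-intervention interactions in the mixed-effect models". No outcome is named and none is excluded.

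The secondary outcomes are CMSS, SF-12, "the Participant Global Impression of Change (PGIC) [52] and the DD". Their timing differs, as the section on time points of outcome measurements shows. For four of the measures it reads: "The VAS, CMSS, SF-12 and DD will be recorded at baseline and at every menstrual cycle throughout the treatment and the follow-up periods". PGIC has its own sentence and no baseline: "The PGIC will be measured at the first, second, third, fourth, fifth and sixth menstrual cycles after inclusion". A general sentence in the abstract reads otherwise, "All assessments will be performed at baseline, each menstrual cycle during the treatment course and the follow-up course", but the Methods section is the specific schedule and leaves PGIC out of the baseline list.

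**The concern.** In a model that includes baseline, randomised arms start level, so a treatment effect appears as a difference that opens up after baseline. The interaction picks that up. PGIC has no pre-treatment point, and each rating already expresses change, so the question of interest is whether the arms differ in PGIC level. The interaction does not ask that. Its null hypothesis is that the arm difference is the same at every cycle from 1 to 6, and a steady benefit satisfies this exactly.

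If the rule were followed for PGIC, a stable perceived benefit would usually be reported as no difference. A significant result would show that the difference grows or fades, and could be misread as showing its size. The trial's stated aim is to separate the specific effect (AHP-APP) from the non-specific effect (APP-WL), so the pairwise contrasts are the ones that matter.

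**Working it through.** **1. The plan's own figure.** The sample size section assumes VAS decreases of 38, 29 and 26 mm with SD 20 mm. The mean is 31 and the SD of the three means is √[(7² + 2² + 5²)/3] = √26 = 5.099. So f = 5.099/20 = 0.255, as stated. A three-group one-way ANOVA has power 0.796 at 50 per group and 0.805 at 51, so 51 is reproduced; 51/0.85 = 60 per group and 180 in total. This calculation concerns VAS, not PGIC. It is used here only as a source of effect sizes: AHP-APP (38 − 29)/20 = 0.45 SD and APP-WL (29 − 26)/20 = 0.15 SD.

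**2. What the interaction tests.** Let δₜ be the difference between two arms at cycle t.
- PGIC, t = 1 to 6: the interaction null is δ₁ = … = δ₆ (5 df), or zero slope of δₜ if time is linear. If δₜ = δ at every cycle, the null is true for any δ, and the rejection rate equals alpha, 5%.
- Outcome with baseline, t = 0 to 6: δ₀ = 0 by randomisation. If δ₁ = … = δ₆ = δ, the null fails unless δ = 0.

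**3. Simulation.** 3,000 two-arm trials per setting, with equal correlation ρ between cycles, on a continuous score and on an assumed 7-level score. The effect size, ρ and number of levels are assumptions; the protocol gives none of them for PGIC.

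| Setting | Interaction rejects | Arm difference in six-cycle mean |
|---|---|---|
| Constant 0.45 SD, 51 per arm, ρ 0.3-0.7 | 4.5-5.4% | 73-93% |
| Constant 0.45 SD, 60 per arm, ρ 0.3-0.7 | 4.7-5.8% | 80-97% |
| Constant 0.9 SD, 51 per arm, ρ 0.5 | 4.8-5.4% | 100% |
| 0.45 SD at cycles 1-3, zero at 4-6, 51 per arm, ρ 0.5 | 86% (categorical time), 93% (linear) | 31% |
| Builds 0.15, 0.30, 0.45, then stays, 51 per arm, ρ 0.5 | 27% (categorical), 36% (linear) | 68% |

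For comparison, when a baseline point is added and the same 0.45 SD effect follows it, the categorical interaction rejects in 39-81% at 51 per arm. The missing baseline is therefore the cause.

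**4. The smaller contrast.** The mean of k equally correlated ratings has variance v = [1 + (k − 1)ρ]/k in SD² units, and the noncentrality is d/√(2v/n). With k = 6, d = 0.15 and n = 60:
- ρ = 0.3: v = 0.417, noncentrality 1.27, power 24%.
- ρ = 0.5: v = 0.583, noncentrality 1.08, power 19%.
- ρ = 0.7: v = 0.750, noncentrality 0.95, power 16%.

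**5. Averaging over cycles 1-3 only.** The same formula with k = 3, d = 0.45 and ρ = 0.3 to 0.7 gives v = 0.533 to 0.800 and power of 87% down to 71% at 51 per arm, and 92% down to 78% at 60 per arm. At 0.15 SD and 60 per arm it gives 20% down to 15%.

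**6. The three-group test.** For the group term of the repeated-measures ANOVA on the six-cycle mean, with f = 0.255 and 51 per group, the noncentrality is 3 × 51 × f²/v. Power is 99%, 96% and 91% at ρ = 0.3, 0.5 and 0.7.

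**The case against.** The protocol never says that PGIC will be tested by the interaction. The rule speaks of change, and the Discussion says "we will compare the change in menstrual pain after administration of three interventions", so it can be read as change from baseline in outcomes that have one. The paired before-after t test in the same section cannot be computed for PGIC either, which suggests text written for before-after outcomes. This stands, and it makes the point conditional. It does not remove it: the interaction is the only pairwise rule given, it has no limit by outcome, and PGIC is literally a rating of change. If PGIC is outside the rule, the stated pairwise plan does not cover it, and the same clarification is needed.

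The repeated-measures ANOVA also stands. Its group term would detect a constant overall difference, so a reader should not infer that the plan is blind to a PGIC benefit. But it is an omnibus test that a difference between AHP and WL alone could make significant, so it does not separate the two contrasts.

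A benefit equal at all six cycles is one pattern among several, since treatment stops after cycle 3. If the benefit fades, the interaction rejects more often, but because of the fading; it still does not estimate the PGIC level.

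A reader might also infer a large loss of power in both contrasts. The protocol's own VAS figures do not support that for APP-WL, where even a direct comparison is weak.

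**Conclusion.** The point holds in conditional form. If the stated pairwise rule is applied to PGIC, it targets the wrong quantity, and a constant benefit is declared significant in about 5% of trials. That figure follows from the model and depends on neither the effect size nor the correlation.

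The power forgone does rest on assumptions: VAS effects carried over to PGIC, equal correlation of 0.3-0.7, and a benefit constant over six cycles. Against about 5% for the interaction, a direct six-cycle comparison has about 73-97% for AHP-APP at 51-60 per arm, a loss of roughly 68-92 percentage points. For APP-WL at 60 per arm it has about 16-24%, a loss of roughly 11-19 points.

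The documents do not support saying that the protocol definitely plans this test for PGIC, or that the primary analysis is affected: VAS has a baseline. This is a correction worth making to the analysis of one secondary outcome.

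**What to change.** In the methods of statistical analyses, limit the time-by-intervention rule to outcomes with a baseline value (VAS, CMSS, SF-12, DD). For PGIC, state that AHP-APP and APP-WL are compared in level, as the arm contrast from a mixed or ordinal model with arm, cycle and arm-by-cycle terms, averaged over pre-specified cycles. One option is to average over treatment cycles 1-3 and report cycles 4-6 separately as follow-up. The choice matters: if the benefit ends with treatment, the six-cycle mean has only 31% power in the setting above. With k = 3, d = 0.45, ρ = 0.5 and 51 per arm, the formula in step 4 gives v = 0.667 and 79% for the cycle 1-3 mean. Keep the interaction to describe whether the difference changes over time.

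The cost is a sentence or two of wording and a separate model for PGIC. No extra data, visits or participants are needed. The article reports recruitment as ongoing; the change should be fixed before allocation is revealed.
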